### Research objectives and hypothesis

The purpose of this study is twofold: first, to determine the effectiveness of four mixed modalities, namely Mixed ABC, A + B, C + A, and B + C, of three training programs (A: cognitive training, B: physical training, and C: combined cognitive and physical training (CCPT)) on cognition, fitness, and psychosocial-related health of community-dwelling older adults in Hong Kong; and second, to determine which specific training program being most effective among the three programs as compared to the control group (CG).

The hypothesis is that participants with the integrated format of three training modes will have higher cognition and fitness scores than the participants with the other combinations of two training modes, and all these mixed modalities will show greater positive outcomes than the control group.

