## Methods

### Research design

This study is a cluster randomized controlled trial (CRCT), to be carried out in 20 community elderly centres (see Fig. 1). The elderly centres will be randomly selected from the population list of elderly service providers in the 18 districts of Hong Kong and assigned to either one of the 4 Intervention Groups (IGs) or the Control Group (CG). There will be 16 centres in the IGs and 4 centres in the CG participating in a 6-months program (4-month intervention with 2-month follow-up). The 20 participating centres will be equally allocated to two Phases, I and II, with each Phase involving 8 centres in IGs and 2 centres in CG. Each IG will be randomly assigned to one of the four combinations of three training modes that include cognitive (A), physical (B), and combined cognitive and physical training (CCPT, i.e. C), namely Mixed ABC, A + B, C + A, B + C. The intervention will last for 4 months in which the training is conducted for 16 sessions, 2 sessions per week, and 60 min per session.

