**Fig. 1 Fig1:**
[figure not shown]
Flow diagram of the study through two phases of the CRCT, including recruitment, allocation, intervention, and data collections points

In each phase, four repeated assessments (T1-T4) will be conducted: T1 is the pre-test before intervention; T2 and T3 will be conducted on intervention right after the end of 2-month and 4-month, respectively; T4 is a follow-up test conducted 2 months after the completion of all intervention training. Participants of CG will be asked to assume regular-daily habitual activities and take four repeated assessments only.

The study is designed in accordance with the SPIRIT (Standard Protocol Items: Recommendations for Interventional Trials). The study protocol has been approved by University Research Ethics Committee (REC/19–20/0066) and registered at ClinicalTrials.gov Identifier: NCT04727450.

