### Interventions

Each selected elderly centre will be randomly assigned to either IGs or CG and asked to help to recruit participants with a sample size of 14–15 older adults. There will be 16 centres in the IGs to receive four combinations of three training modes (A: cognitive training only, B: physical training only, C: CCPT) and with 4 centres in IGs. The four types of combinations are 1. Mixed ABC, 2. A + B, 3. B + C, 4. C + A, matched with 4 CGs in total. For the case of combination 1. Mixed ABC, participants will receive different training modes every 2 consecutive weeks with randomized order. For the case of combinations 2, 3, and 4, the participants’ centres will receive an assigned sequential order of two training modes with each mode lasting for 2 months. All participants of IGs will attend training sessions twice a week, and 60 min duration per session (per mode). The random allocation sequence of intervention was generated by a blinded statistician external to the research team. Due to the nature of each intervention, blinding cannot be applied to the participants, while the blinded group allocation will be applied to the data assessors and analysts. Each subject will be identified by the number code. Data from those participants having more than 70% attendance will be analyzed. No further follow-up with missing cases will be done because they will be usually missing at random (such as absences due to doctor’s appointments or being sick).

The three training modes (A, B, and C) are introduced as follows:A: Cognitive training only

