### Statistical analysis plan

Data analysis will be performed using the Statistical Package for social sciences (IBM SPSS ver. 27). All data points that were considered outliers, which are out of the interquartile range (IQR) covering the 50% central of samples, will be excluded from analyses. For analyzing program effects, a mixed-effects ANOVA will be used. In this model, there will be a between-subjects factor consisting of five groups (CGs = 0, IGs = 1 to 4) and a within-subject factor consisting of four Trials (Time = 1 to 4). The dependent variables will be the outcome measures of the three cognitive tests and the five physical fitness tests. The independent variables will be time (1 pre-test, 2 post-tests, and 1 follow-up) and intervention (IGs with 4 combinations of training modes & CGs). The participating elderly centre as a cluster will be treated as a random effect. Assumptions (normality, sphericity, etc.) for mixed-effects ANOVA will be tested using an alpha level set as 0.05. The focus of this mixed-effects ANOVA will be mainly on the between-group differences, i.e., the differences among the four IGs. Post-hoc comparisons among IGs will be conducted with Bonferroni correction after finding significant effects. Next, for analyzing specific intervention effects in the 3 treatments crossover design, a similar mixed-effects ANOVA will be used. In this second model, there will be one within-subject factor of four repeated trials (Time = 1 to 4). The dependent variables will be the outcome measures of the three cognitive tests and the four physical fitness tests. The independent variables of time (pre-test, 2 post-tests, and follow-up) and three training modes will be examined by ANOVA with repeated measures. The focus of the second model is to examine the individual effect of the three training modes, so a pre-planned contrast will be conducted to examine their effects. Based on these statistical analyses, results and conclusions will be drawn.

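### The crossover model for ranking training modes A, B and C has no washout and names no carry-over term, so its mode contrasts are biased if first-mode gains persist and differ between modes

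*Protocol article*

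**What the plan says.** The second objective (Research objectives and hypothesis) is to find which of the three programmes works best, with the control group (CG) as comparator. The Statistical analysis plan section gives it a model of its own: "for analyzing specific intervention effects in the 3 treatments crossover design, a similar mixed-effects ANOVA will be used". The terms follow: "The independent variables of time (pre-test, 2 post-tests, and follow-up) and three training modes will be examined by ANOVA with repeated measures". So does the target: "The focus of the second model is to examine the individual effect of the three training modes, so a pre-planned contrast will be conducted". No sequence, preceding-mode or carry-over term is named, and no sentence assumes that carry-over is absent.

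On the schedule, the Interventions section says that centres in A + B, B + C and C + A "will receive an assigned sequential order of two training modes with each mode lasting for 2 months". It does not say whether each pair runs in one order or in both. Research design gives a total intervention length of 4 months. On assessments, "T2 and T3 will be conducted on intervention right after the end of 2-month and 4-month, respectively", and "T4 is a follow-up test conducted 2 months after the completion of all intervention training". Mixed ABC changes mode every two weeks but is assessed at the same visits.

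**The concern.** A crossover comparison credits each period's result to the treatment given in that period. That is sound only if the earlier treatment's effect has gone, or is modelled. Here the second mode starts when the first ends. The outcomes are cognitive performance and fitness, where gains need not vanish at the switch, and the trial schedules a test two months after training. T3 may then hold the second mode's gain plus whatever is left of the first mode's. A model with time and current mode can place the remainder only in the visit effect, which absorbs the part common to all modes, or in the second mode's effect, which takes the rest. At stake is the answer to a named objective: differences between modes may be understated and, under some orders, the wrong mode may come out ahead.

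**Working it through.** **The plan's own figure.** The stated sample size reproduces: 95 × (1 + 14 × 0.1) = 95 × 2.4 = 228, and 228 / 0.8 = 285. It is sized for the five-group by four-time analysis. No figure is given for the second model.

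**Washout.** 4 − (2 + 2) = 0 months, with T2 at the switch and T3 at the end. (The session count stated next to the 4 months, 16 at two a week, covers 8 weeks. Those passages need reconciling, but this check uses only the months.)

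**Set-up.** The document gives no mode effects, so gains a, b and c (SD units) for A, B and C are assumptions. Let r be the share of the first mode's gain still present at T3. Expected scores are T1 = 0, T2 = first mode's gain, T3 = second mode's gain + r × first mode's gain. Mode is coded as the one currently given. T4 and Mixed ABC are left out: no mode is running at T4, and no visit separates the modes in Mixed ABC.

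**Both orders of each pair, equally used.**
- Without an arm term (none is named for this model), each mode's estimate averages its T2 and T3 results. The contamination is r(b + c)/4 for A and r(a + b)/4 for C, so C minus A changes by −r(c − a)/4. Every contrast shrinks by 0.25r: 12.5% at r = 0.5, 25% at r = 1.
- With an arm (sequence) term, each mode indicator is centred over the three visits of an arm. Each mode occurs in 4 of 6 sequences and each pair of modes in 2, so the information for a contrast is 4(2/3) + 2(1/3) = 10/3. The retained gains contribute −(4/3)r per unit of true difference. Shrinkage is (4/3)/(10/3) × r = 0.4r: 20% at r = 0.5, 40% at r = 1.

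Ranks are kept in both versions.

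**One order per pair, A-B, B-C, C-A (assumed).** B always follows A, C follows B, and A follows C. With an arm term the same algebra gives an estimated C minus A of (c − a) + r(0.2a + 0.4b − 0.6c).

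| Assumed a, b, c | True C − A | r = 0.5 | r = 1 |
|---|---|---|---|
| 0.2, 0.1, 0.4 | +0.20 | +0.12 | +0.04 |
| 0.3, 0.1, 0.4 | +0.10 | +0.03 | −0.04 |
| 0.3, 0.1, 0.35 | +0.05 | −0.005 | −0.06 |

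Without an arm term the bias is r(b − c)/2. The second row at r = 1 becomes 0.10 − 0.15 = −0.05, also a reversal.

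**Other orders.** For the reverse cycle (B-A, C-B, A-C) with an arm term, the bias in C minus A is r(0.6a − 0.4b − 0.2c). The second row at r = 1 gives 0.10 + 0.06 = +0.16, so C stays ahead. With gains 0.2, 0.1, 0.4 the same cycle leaves C minus A at 0.20 but returns A minus B = −0.04 against a true +0.10. The effect on ranks therefore depends on the order.

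**No-bias cases.** At r = 0 every bias term is zero. If a = b = c, each bracket sums to zero. Adding a preceding-mode term returned the true contrasts in every case tried.

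**Cost of using only the first period.** Assume 4 of the 12 two-mode centres start with each mode: 4 × 14.25 = 57 people; × 0.8 = 45.6; / 2.4 = 19 effective. By the normal approximation without baseline adjustment, z = d√(19/2) − 1.96. For d = 0.35 this is 1.08 − 1.96 = −0.88, power about 19%. For d = 0.5 it is 1.54 − 1.96 = −0.42, power about 34%.

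**Interval width.** With ICC 0.1, 228/20 = 11.4 analysed per centre, rho 0.5 and an assumed centre autocorrelation of 0.5 to 0.8, the standard error of C minus A is about 0.13 to 0.16 SD as written, and 0.17 to 0.19 with a carry-over term and both orders. From these rounded values, 1 − 0.16/0.19 = 16% and 1 − 0.13/0.17 = 24%.

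**The case against.** **The coding of mode at T3 is not stated.** This is correct. If a participant were coded as having received every mode so far, then with both orders and an arm term the contrasts are unbiased at any r. With the single cycle they are unbiased only at full retention. Current-mode coding is the natural reading of a crossover, but it is not certain. The point stands as a conditional one.

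**A reader might infer that the ranking of modes is wrong as planned.** The documents do not support that. Bias needs gains that are both retained and unequal, and a false winner also needs particular unbalanced orders, which the Interventions section does not state. With both orders, ranks hold.

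**A reader might also infer that the intervals are far too narrow because a first-period analysis gives much wider ones.** Most of that gap comes from discarding T3. Only the comparison with a carry-over model on the same visits is like for like, and it gives roughly 16 to 24%.

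**The article condenses a fuller plan, and the stated hypothesis concerns the combinations.** The second part stands: the hypothesis is served by the first model, which limits the severity. The first part does not dispose of the point, because the article names the design, the independent variables and the contrast. What it states does not suit the objective it serves.

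**Conclusion.** The concern holds in conditional form. The article fixes a crossover analysis for back-to-back modes with zero washout and lists only time and mode as terms. If first-mode gains persist to T3, differ between modes, and T3 is coded by current mode, the mode contrasts are biased. Retention is plausible for these outcomes, and unequal effects are what the objective looks for. With balanced orders the size is 20% or 40% shrinkage (arm term) or 12.5% or 25% (no arm term) at half or full retention. With one order per pair, a reversal such as −0.04 against a true +0.10 is possible under assumed gains. Nothing is wrong if r = 0 or the modes are equal. The group-by-time model and the 285 are not touched. Severity: should be fixed, since it affects the second objective only and the data remain re-analysable.

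**What to change.** Leave the training schedule alone and change the analysis text:

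- Drop the crossover label. State which sequences were assigned and how mode is coded at each visit.
- In the two-mode arms, estimate mode effects from T2 adjusted for T1, grouped by first mode, with CG as reference and centre as a random effect. Alternatively or in addition, model T1 to T3 with a preceding-mode (carry-over) term.
- Report T3 as the effect of the ordered pair.
- Leave Mixed ABC and T4 out of the mode contrast.
- Label the ranking of modes exploratory.

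The cost is rewording and a different model on data already planned, with wider intervals. With one order per pair, the current mode at T3 determines the preceding one, so the carry-over model adds nothing to the first period. Power is then roughly 19% at d = 0.35 and 34% at d = 0.5; adjusting for T1 would raise this somewhat. That precision is what the design offers without assuming zero carry-over.

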## Discussion

The elderly population worldwide is expected to increase exponentially. There will be a higher percentage of elder adults increasing in Hong Kong in the coming decades which will be associated with more population suffering from cognitive and fitness decline. The growing aging population will also have a significant impact on the public finances including social healthcare costs and medical expenses. Thus, it is necessary to conduct programs to postpone the functional decline and promote the concept of ‘healthy aging’ among the elderly community. From the previous literature, the benefits of cognitive and/or physical exercise training have been well documented. However, how a combination of these training might benefit the cognitive functions, physical fitness, psycho-related health of community-dwelling older adults in Hong Kong remains unclear. This study takes a holistic approach to provide a detailed account of the implementation and evaluation of cognitive and/or fitness training intervention and is expected to see the multifaceted effects of the varied combination of training modes on the elderly’s health.

If the intervention programs would be proven to be effective, the immediate impact will be those community-dwelling elder adults joining the programs would not only increase cognitive and physical health but also provide practice models to develop similar structural programs providing elderly populations with psychosocial support. The concept of ‘healthy aging’ could be promoted to the general population by exposing the study to publicity. The program used in this study can be further explored to be promoted to other sectors of society so that a higher number of older adults can benefit from the program. The results can provide further evidence for the government departments including the Elderly Commission in Hong Kong or other overseas regions to implement new social policy, such as allocating more financial support for the non-government organization to set up local training centres to offer effective cognitive-cum-physical game-oriented activities. Therefore, the number of older adults being frail and having early loss of functional independence and disability will be decreased due to a reduction of the percentage of them having a cognitive and physical decline.

These significant impacts will transfer to a reduction in the public healthcare cost associated with frailty, cognitive and mental problems in the aging society of Hong Kong and worldwide. When more elderly populations consistently engage in the training for several years, they would realize the importance of self-responsibility and a healthy lifestyle in their own health maintenance, which would be a long-term impact on human society.

## Data Availability

Not applicable.

## Abbreviations

ACSM: The American College of Sports Medicine
RCT: Randomized controlled trial
WHO: World Health Organization
NIH: National Institutes of Health
SPIRIT: Standard Protocol Items: Recommendations for Interventional Trials
BIGMAP: Brain Invigoration Gross Motor Activation Program
BMI: Body mass index
IG: Intervention group
CG: Control group
A: Cognitive training
B: Physical training
CCPT: Combined cognitive and physical training
REC: Research Ethics Committee
SD: Standard deviation
MoCA: Montreal cognitive assessment test
CES-D: The center for epidemiological studies-depression
CTT: Color trial test
WCST: Wisconsin card sorting test
RBMT: Rivermead behavioral memory test
ANOVA: Analysis of variance
